#### Non-operative treatment

The participants destined for non-operative treatment, either through allocation to the non-operative group or as a result of allocation to the individualized treatment algorithm, are treated with a circular below-the-knee cast from the time of the first appointment in the outpatient clinic. The ankle is held at maximal, unforced plantar flexion. Weight bearing is not allowed and crutches are obligatory. After 3 weeks from initiated treatment in the emergency department the cast is removed in the outpatient clinic and the injured leg is transferred to a functional brace (Walker boot) with three heel wedges promoting 20° plantar flexion over the ankle. The wedges are inspired by the Breg Achilles wedges and reach from the heel to the metatarsal bones. They come in two sizes, medium (length 15 cm and height 2 cm each) and large (length 19 cm and height 2.5 cm each).

The patient will follow standard rehabilitation and the follow-up evaluations.

#### Operative treatment

Participants destined for operative treatment, either through allocation to the operative group or as a result of allocation to the individualized treatment algorithm, are operated on within 14 days of the rupture. The procedure is performed under local anesthesia with the patient in the prone position. Preoperatively, 2 g of IV dicloxacillin are administered. An incision of approximately 5 cm is placed over the rupture site just medial to the midline. The peritendium is reached by stump dissection and is kept intact (Fig. 4). The rupture is palpated through the peritendium and a transverse incision is made to expose the rupture if needed. The tendon stumps are drawn into the transverse incision and two modified Kessler sutures (Fiber-wire®, Arthrex size 2) are used to fix the tendon approximately 4 cm proximal and distally to the transverse incision. The ankle is placed in maximal, unforced plantar flexion before the sutures are tightened maximally, bringing the tendon stumps together inside the peritendium. The peritendium is closed with Vicryl, Ethicon 2–0 (Fig. 4) [4]. After tensioning of the sutures, the ankle must be in an equinus position comparable with the uninjured leg or re-suturing needs to be performed. The skin is closed using single madras sutures. The lower leg is then placed in a circular below-the-knee cast with the ankle held at maximal comfortable plantar flexion. Weight bearing is not allowed and crutches are obligatory for the following 3 weeks. After 3 weeks from operative treatment the cast is removed in the outpatient clinic and the injured leg is transferred to a functional brace (Walker boot) with three heel wedges promoting 20° plantar flexion over the ankle (the same as for the non-operative treatment).

**Fig. 4 Fig4:**
[figure not shown]
Illustration of the peritendium sparring surgical technique. **a** An incision of approximately 5 cm is placed over the rupture site. The peritendium is reached by careful stump dissection and is kept intact. **b** A transverse incision is made at the rupture site to expose the rupture. **c** The tendon stumps are drawn into the transverse incision and two modified Kessler sutures (Fiber-wire®, Arthrex size 2) are used to fix the tendon approximately 4 cm proximal and distal to the transverse incision. **d** The peritendium is closed with Vicryl, Ethicon 2–0 and the ankle is placed in maximal, unforced plantar flexion before the sutures are tightened maximally, bringing the tendon stumps together inside the peritendium. **e** A schematic drawing of the double Fiber-wire®, Arthrex size 2 a.m. Kessler with modification in terms of knots proximally on the sides

The participants will follow standard rehabilitation and the follow-up evaluations.

#### Rehabilitation

All participants in the trial are treated similarly in all aspects except for the initial operative or non-operative treatment.

#### Three weeks after surgery or 3 weeks after the non-operative treatment is started

Participants are seen in the outpatient clinic and the cast is removed. Sutures are removed for operatively treated patients. The leg is placed in the functional brace (Walker boot) with three heel wedges promoting 20° plantar flexion over the ankle. The participants are instructed to remove the consecutive two wedges after 2 and 4 weeks, respectively, and encouraged to start partial weight bearing of approximately 10–15 kg load from weeks 4 to 7 and full weight bearing from week 8. The brace must be kept on during sleep but can be removed during bathing if the leg can be kept completely off-loaded.

#### Nine weeks after surgery or 9 weeks after the non-operative treatment is started

At 9 weeks, the functional brace is removed and the tendon is examined by the physiotherapist. If the tendon has heeled as expected, exercises are started. The participants are recommended to use shoes with a heel wedge of minimum 10 mm until 4 months after the injury. Compression stockings of 15–20 mmHg (“Jobst active wear/ulcer”) are recommended for 6 months. At weeks 9–13 the participants are instructed to perform a written home exercise program two times every day. The program includes six exercises: the first two exercises have the purpose of increasing the range of motion in the ankle joint (pro- and supination and dorsal-plantar flexion 3 × 10 repetitions each), loaded motion over the ankle in plantar flexion with resistance from an elastic band (3 × 10 repetitions), side laying hip abduction (to activate m. gluteus medius, 2 × 15 repetitions), standing heel lift (3 × 10 repetitions), balance training (one leg stand 3 × 30 seconds). The participants are referred to continued rehabilitation in the municipality from week 13. To increase compliance the physiotherapists in the municipality are given written instructions on which exercises are recommended (progressive exercises for increased muscle strength, proprioception and balance in the ankle and leg, and training of walking ability). Prior to the start of the trial, all collaborating municipalities were invited to a meeting, where the rehabilitation process was described in depth by a physiotherapist and orthopedic surgeon at their hospital.

Instructions given to the participants at 9 weeks:
Avoid total dorsiflexion with weight bearing. When dorsal flexing the ankle in standing, the vertical line from patella shall land behind the front line of the toes. Without weight bearing the patients are allowed to dorsiflex until the tendon is tightened.Use compression socks during daytime.If encountering problems with a swollen ankle or pain, take a break during the day, with the foot elevated.Rest if pain in the tendon.Walk with the crutches, as long as the patient is limping while walking.The participants are transferred to shoes for weight bearing for a minimum of 2 months with 1 cm heel rise. In running shoes with 1 cm heel lift an addition heel rise is not applicable.Cycling on a stationary bike can start immediately after the walker is removed. The pedal should be placed under the middle of the foot the first 2 months. Biking outside is allowed 12 weeks after injury.Swimming is allowed 11 weeks after injury (with great care getting into the water).Car driving is allowed 11 weeks after injury if the patient has injured the left leg and after 13 weeks if it is the right leg that is injured.

At 16 weeks, running on soft, even surfaces can be started slowly, if the participants can walk 5 m on tip-toe and perform five consecutive single heel rises on the injured leg (at 90% of the height of the uninjured leg). After 6–9 months, the participants can slowly start returning to contact sports but postpone participation in match and competition till after 12 months.

Concomitant care permitted or prohibited does not differ between the intervention groups.

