### Primary outcome measure

The primary outcome is the heel-rise work test, which is an endurance test where the participant stands on one leg and lifts the heel up and down until exhaustion [18]. The number of heel rises is counted and the height measured and plotted into a diagram on the x-axis and y-axis, respectively. Based on the weight of the participant the total work is estimated as area under the curve. The heel lift distance between the heel and the floor is measured in millimeters. The procedure is performed on the uninjured leg first and subsequently on the injured leg at 12 months. The participant is barefoot for the heel-rise work test and stands on a flat surface with a 10° inclination. The measurement system MuscleLab (Ergotest Technology, Oslo, Norway) is used at all the centers for these functional tests. The tests are developed by the Gothenburg group [18]. The metric for both the primary outcome measure as well as all the secondary outcomes is value at time point, meaning that it is the difference at a point in time between groups that will be assessed. The method of aggregation (how data from each group will be summarized) will be equal for all three groups and will be either mean, median, percent, or proportion depending on the results.

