### Secondary outcome measures

The secondary outcome measures are listed below (the timing of the assessments is shown in Fig. 1).
Copenhagen Achilles Length Measure (CALM) [19] is an ultrasonographic measurement of tendon elongation. It comprises two measurements (Fig. 2): the total length of the Achilles tendon (free tendon and fascia) and the free length of the Achilles tendon. The measurements are preformed the same way; they have the same distal landmark but the proximal landmark differs. CALM has shown good reliability and is recommended over other measurements of elongation [17, 20, 21]. The measure is performed as described by Barfod et al. but with the feet of the patient (laying in the prone position) hanging free of the table instead of with 10° degrees of plantar flexion in the ankle joints as originally described [16, 21]. Landmarks are identified and marked on the skin. The distal landmark is the posterior and most superior part of the calcaneus in the midline, which on sagittal ultrasound examination is identified as the point where the cortical bone and its underlying shadow end. The proximal landmark for the total length of the Achilles tendon is the distal tip of the medial gastrocnemius head, which on sagittal ultrasound examination is recognized as the point where the most distal muscular fibers are inserted into the deep crural fascia. The proximal landmark for the free length of the Achilles tendon is the distal tip of the soleus muscle, which is defined at the point where the most distal muscular fibers insert into the Achilles tendon. The distance between these two points on the un-injured leg defines the total length of the Achilles tendon and the free length of the Achilles tendon, respectively. The differences between the non-injured and the injured leg are defined as tendon elongation. At inclusion only the total Achilles tendon length is measured for both legs. The examination of both the total and the free part of the tendon of both the injured and un-injured leg is performed at 6- and 12-month follow-up. The position of the feet also differs between inclusion and follow-up. During inclusion, the originally described position of the feet is used (10° of plantar flexion in the ankle joints) but during the 6- and 12-month follow-up, the feet hang free of the table.Heel-rise work test: The test is conducted as described for the primary endpoint and conducted as a secondary endpoint at 6 months.Achilles tendon resting angle (ATRA) [22]: ATRA is an indirect measurement of tendon elongation. The patient lies flat in the prone position on the examination bed. The knee is flexed at 90 degrees and the ankle sits in a relaxed position. The ATRA is determined as the angle between the longitudinal axis of corpus of the fibula and the longitudinal axis of corpus of the fifth metatarsus. ATRA is determined for both the injured and the uninjured leg. The difference between the healthy and the injured leg is evaluated. ATRA has shown excellent reliability [22, 23].Complications: Incidence rates of the commonly known complications and adverse events such as infection, re-rupture, permanent sural nerve dysfunction, deep venous thrombosis, adhesions, and pain at the scar are noted. Attention is also paid to unknown complications in relation to the treatments.Achilles tendon Total Rupture Score (ATRS) [24]: Patients fill out the ATRS questionnaire at inclusion and after 6 and 12 months in connection with the follow-up visits in the outpatient clinic. ATRS is a patient-reported outcome measure developed to assess symptoms and physical activity after treatment for acute Achilles tendon rupture. The Danish version was found to have good validity and be reliable to use for comparison on the group level [25].Tegner Activity Scale: A scale that aims to provide a standardized method of grading work and sporting activities. Tegner activity scale is a graduated list of activities of daily living, recreation, and competitive sports. The patient is asked to select the level of participation that best describes their level of activity at inclusion and at 6 and 12 months after rupture and before injury [26].Calf circumference: The patient sits on an examination bed with legs hanging down. The circumference of the calf is measured using a measuring tape (13 cm under apex patella).MRI: MRI of the calf is performed after 1 year for the first 60 patients included at Copenhagen University Hospital Amager-Hvidovre. MRI will be conducted to obtain a deeper understanding of changes to the different structures in the muscle–tendon complex during the first year after rupture. The MRI will be conducted at Copenhagen University Hospital Amager-Hvidovre in an Acanto 1.5 T scanner. Both lower legs will be scanned.Gait analysis: Gait analysis is performed after 6 and 12 months for the first 60 patients included at Copenhagen University Hospital Amager-Hvidovre. The gait analysis will be conducted at the Gait Laboratory, Copenhagen University Hospital Amager-Hvidovre. Twenty-two reflective markers are placed on the patient’s skin with tape on specific anatomical locations, as described by Speedtsberg et al. [27]. The participants are instructed to walk barefoot at a self-selected speed on a 10-m level walkway. The reflective markers are filmed by eight infrared cameras, whereby the joint angles during gait are measured. In combination with the ground reaction forces from two force plates embedded in the floor, the joint moments and powers will be calculated.

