#### Analysis of endpoints

Demographic parameters will be presented for each treatment group with mean and standard deviation (SD) or median and interquartile range (IQR) for continuous parameters and frequencies and percentages for categorical parameters.

Difference in Heel-rise work test will be tested by *t*-test or, if data can’t be assumed to be normally distributed, Wilcoxon sum rank test. Test will be made for the comparison individual vs operative treatment and individual vs non-operative treatment. To account for possible confounders, a linear regression will also be fitted for each comparison. Confounders include, but are not limited to, sex, age, BMI, and ATRS pre-injury; the confounding effect of these variables will be evaluated in the model by including and removing the variable and evaluating the change between the treatment group estimates.

Differences in severe complications (yes/no) between individual and operative treatment will be tested by chi-square test or, if the amount of expected observations for a single combination is less than 5, Fishers exact test. Additionally, the test will be adjusted for possible confounders in a logistic regression model; possible confounders and evaluation of these will be done as described in the Heel-rise work test models. Similar tests and models are made for the comparison of individual and non-operative treatments. Differences between individual and operative treatment and individual and non-operative treatment for all other secondary outcomes will be tested by *t*-test or Wilcoxon sum rank test.

All analysis will be done as intention-to-treat (ITT), that is, each patient is analyzed according to the treatment group they are randomized to. The results will therefore be interpreted as the effect of offering the patient the specific treatment options, regardless of if they complete them or not. Missing data will be imputed by multiple imputation, with imputation models based on available variables believed to be predictive of the missing measures. Additionally, the analysis for the primary outcome will be conducted as per protocol analysis, with per protocol defined as patients complying with the assigned protocol.

No interim analyses will be done.

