An Achilles tendon rupture is an injury that affects the physical function of the patient to a large extent. Therefore, the present trial has chosen a functional outcome as the primary outcome. In contrast, several previous randomized controlled trials have used patient-reported outcome measures as primary outcomes [4, 12, 31]. However, their results have shown the patients to have an acceptable score within the patient reported outcome measures but markedly low scores among the tests of physical function. An example is Olsson et al. [4], having a median ATRS value of 89 points (100 being top score) but the heel-rise work test showed the injured leg performing at 45% compared to the non-injured leg. Having a functional outcome as primary outcome might, therefore, detect the functional deficits post-injury that the patient-reported outcome measures are not always able to capture.

The power of 0.9 and having two control groups is a strength within the design. To complete the trial within a reasonable time span and to improve the external validity of the trial, a multi-center setup was chosen. The improved external validity makes the results easier to implement and generalize.

When designing this trial, we prioritized a set up that would be feasible to implement into clinical practice. Therefore, the patients are following the initial standardized treatment plans at the hospital and then continue the rehabilitation and exercise program together with the physiotherapists in the municipality from week 13. Each of the hospitals in the study collaborates with up to 11 different municipalities and some patients also decide to visit a private physiotherapist. Before starting the project, all collaborating municipalities were invited to a meeting where information was given about the study and where a description of the rehabilitation program was provided as well as suggested exercises with progression were proposed. So even though we could not control the rehabilitation from week 13, we did try to advise the collaborating physiotherapists.

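### The Tegner comparison is planned without adjustment for the pre-injury level the trial already collects, and its 12-month result needs a stated limit because all participants are advised against competition until then

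*Protocol article*

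**What the plan says.** Four places in the protocol article bear on this.

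- **Secondary outcome measures.** The scale reaches into competition: "Tegner activity scale is a graduated list of activities of daily living, recreation, and competitive sports". Participants choose the level that "best describes their level of activity at inclusion and at 6 and 12 months after rupture and before injury". A pre-injury level is therefore on file for each participant.
- **Primary outcome measure.** The article fixes the metric for every outcome: "The metric for both the primary outcome measure as well as all the secondary outcomes is value at time point".
- **Analysis of endpoints.** Adjusted models are described for heel-rise work (linear regression) and severe complications (logistic regression). Pre-injury ATRS is among the named covariates. The two contrasts "for all other secondary outcomes will be tested by *t*-test or Wilcoxon sum rank test", and Tegner belongs to this group.
- **Nine weeks after surgery or 9 weeks after the non-operative treatment is started.** After 6 to 9 months, "the participants can slowly start returning to contact sports but postpone participation in match and competition till after 12 months". The section adds: "Concomitant care permitted or prohibited does not differ between the intervention groups".

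The follow-up section names visits at 6 and 12 months and none later. No section links the advice on competition to how a Tegner score is to be read.

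**The concern.** There are two separate issues, and they need separate remedies.

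**Precision.** Activity level differs widely between people before any tendon ruptures. A comparison of raw 12-month scores carries that spread as noise, and a pre-injury rating on the same scale is the natural variable to absorb it. The plan collects the rating and leaves it out of the comparison.

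**Interpretation.** At its upper end the scale records what a participant does, and the protocol advises participants not to do it until after the last visit. In that range a low score may reflect the advice rather than the tendon. A difference between arms among people who would otherwise be competing by 12 months would be partly hidden. A null 12-month Tegner result could then be taken as equal return to activity when the instrument had little chance of showing a difference at the top.

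**Working it through.** **Step 1. The plan's own figure.** The only sample-size calculation is for heel-rise work: N = 2 × (1.96 + 1.281)² × 20² / 10² = 84.03, stated as 84 per group. It reproduces. It does not concern Tegner, for which the article gives no SD, target difference or power.

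**Step 2. Timing of the ratings against the advice.**

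- Before injury: no advice in force.
- Inclusion: within 4 days of injury, leg in a cast, no weight bearing.
- 6 months and 12 months: competition advised against until after 12 months.

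The pre-injury rating is the only one that reflects unrestricted activity.

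**Step 3. Gain from adjustment.** For a linear model with one baseline covariate that has correlation r with the outcome, residual variance is multiplied by 1 − r². The article gives no r, so 0.3 to 0.5 is assumed.

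- r = 0.3: 1 − 0.09 = 0.91
- r = 0.4: 1 − 0.16 = 0.84
- r = 0.5: 1 − 0.25 = 0.75

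The adjusted analysis of 84 per group is then worth about 84 / 0.91 = 92 to 84 / 0.75 = 112 per group analysed without adjustment. If the advice compresses the 12-month scores, r may lie toward the lower end.

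**Step 4. What the ceiling can do.** The documents do not give the share of participants who would otherwise compete by 12 months, the levels that count as competitive, or adherence to the advice. The size of the loss therefore cannot be derived. A simulation on assumed values shows only direction and mechanism. It used an integer score from 0 to 10, latent SD 2, a true shift of 1.0 level, 84 per arm, a lower-arm mean of 3.5 to 5.5, and a cap at level 6 or 7.

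| Adherence to the advice | Observed difference | Power (t-test or Wilcoxon) |
|---|---|---|
| None (no cap) | 0.97 to 0.99 | 0.87 to 0.91 |
| 70% | 0.64 to 0.93 | 0.78 to 0.89 |
| 100% | 0.50 to 0.90 | 0.77 to 0.88 |

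The estimate shrinks more than the power because the cap also narrows the spread. In the most affected setting the lower-arm SD falls from 2.00 to 1.35. The loss grows with the share above the cap: 2% and 7% of the two arms in the mildest setting, 31% and 50% in the most affected.

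**Step 5. Whether step 3 cures step 4.** It does not. Adjustment removes variance explained by the pre-injury level. It cannot recover levels that participants did not report because they followed the advice.

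**The case against.** The strongest case against has four parts.

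1. **The unadjusted test is valid under randomization, and covariate choice for a secondary outcome often sits in an analysis plan.** The validity point stands, so this is a loss of precision and not an error in type I rate. The second part carries less weight here. The article assigns a test to this outcome and reserves regression for two others, so the unadjusted comparison is a stated choice and not a gap.

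2. **The advice is common to all arms, so nothing is biased.** This stands as far as favouring an arm goes. A shared ceiling can only make a true difference look smaller.

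3. **Activity at 12 months under a common regimen is a legitimate outcome, and the article never promises a conclusion on competitive sport.** This also stands. It is why the remedy for the ceiling is a sentence on interpretation and not a new endpoint.

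4. **The advice is not enforced.** A reader might infer that no participant can score a competitive level before 12 months. The text does not support that. The sentence is framed around contact sports, so its reach to other competition is unclear. On later rehabilitation the Discussion says "even though we could not control the rehabilitation from week 13, we did try to advise the collaborating physiotherapists". Competitive ratings become less likely; they are not ruled out.

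A reader might also try to size the loss by supposing that a share p of previously competitive participants contributes no difference. That inflates the required sample by 1/(1 − p)², or 1.23 to 2.78 for p of 0.10 to 0.40. The reasoning fails on three counts: p is not in the documents, such participants can still differ below the ceiling, and the SD shrinks too. In the most affected setting above, the average share above the cap is (0.31 + 0.50)/2 = 0.405, and the formula gives 1/(0.595)² = 2.82. The simulated t-test power falls only from 0.89 to 0.77. By the normal approximation that is a factor of (1.96 + 1.227)²/(1.96 + 0.739)² = about 1.4.

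**Conclusion.** The point holds, and it is modest. The plan fixes an unadjusted Tegner comparison while holding a pre-injury rating that would sharpen it. The gain is a residual variance of 0.91 to 0.75 of the unadjusted value if the correlation is 0.3 to 0.5, which is an assumption. Reduced sensitivity at the top of the scale is real in direction, because all follow-up ratings fall within the period of the advice. Its size cannot be computed from the documents and may be small.

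The problem is confined to one secondary outcome. It favours no arm and leaves heel-rise work and its sample size untouched. A claim that the Tegner result is uninformative, or that the trial is underpowered because of the advice, would go beyond what the documents show.

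**What to change.** 1. In Analysis of endpoints, take Tegner out of the group tested without adjustment. For each of the two planned contrasts, analyse it at 6 and 12 months by linear regression, or by an ordinal model if the distribution calls for one, with the pre-injury Tegner level as a covariate. Keep all randomized participants in the comparison. Use the pre-injury rating recorded at inclusion before allocation is known. The assessment schedule is in a figure that is not shown, so this timing should be confirmed.

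2. Add one sentence saying that the 12-month Tegner result reflects activity under advice on competition common to all arms and will not be used to conclude on return to competitive sport.

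The rehabilitation advice and the visits stay as they are. The cost is analysis wording only, since the pre-injury level is already collected. The price is that no conclusion on competitive sport can be drawn from the 12-month score. The article reports 108 of 300 participants included in February 2020 and no interim analyses, so at that stage the change could be fixed before any outcome comparison.
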